#### Immediate and differed visual and verbal memory

##### Wechsler Memory Scale—Third Edition (WMS–III) Faces

The WMS-III Faces subtest [91] (The Psychological Corporation, 1997) uses a recognition paradigm to assess immediate and delayed visual memory. In Faces I, participants are presented with 24 target faces at a speed of 2 s per picture. Then, they are shown 48 faces (24 targets and 24 distractors) and are asked to identify the target faces by responding either “yes” or “no” to each face. Participants are prompted to keep the target faces in mind. In Faces II, participants are shown 48 faces (24 targets and 24 distractors) after a 30-min delay and are asked to identify the target faces. The Hits–False alarms mean between groups at pretest, posttest, and follow-up assessments will be the outcome of interest. The specific metric will be the change from pretest to posttest and follow-up.

##### Wechsler Memory Scale—Third Edition (WMS–III) Word-Pair List

The WMS-III Word-Pair subtest assesses immediate and delayed verbal memory. In this test, four trials of eight unrelated word pairs are presented at a rate of 3 s per pair. In the immediate recall condition, after the presentation of the four lists, the first word of each pair is read to the participant, who has to provide the associated word of the pair. After a delay of approximately 25–35 min, the same procedure is repeated, and the participant provides the second word of each pair. Finally, a recognition task is administered where 24 word pairs are presented and the participant is asked to identify the pair as either “new” or “old”. The Hits–False alarms mean between groups at pretest, posttest, and follow-up assessments will be the outcome of interest. The specific metric will be the change from pretest to posttest and follow-up.

#### Electrophysiological measures

##### Electroencephalograph acquisition

While performing the experimental memory-based switching task, continuous electroencephalograph (EEG) activity will be recorded using a NuAmps amplifier (Neuroscan Inc.) inside a soundproof, electromagnetically shielded room. We will use a 34-channel elasticized Quik-Cap with Ag/AgCl sintered electrodes (American Medical EEG Association, 1991). To control ocular artifacts, vertical and horizontal electrooculograms will be recorded in two bipolar channels. Eye blinks and vertical eye movements will be monitored via electrodes located below and on the supraorbital ridge of the left eye. Horizontal artifacts will be monitored via electrodes on the outer canthus of each eye. Linked mastoids (A1, A2) will be used as a reference, and participants will be grounded to the AFz electrode. All data will be digitized using a NuAmps amplifier in continuous recording mode. The sampling rate will be 1000 Hz, and all channels will be online bandpass filtered (0.1–140 Hz) and notch filtered (50 Hz) to eliminate power line artifacts. Continuous data will be filtered offline using a digital Butterworth filter (0.1–40 Hz; 12 dB per octave roll-off), an infinite impulse response filter that achieves a given filtering characteristic. After filtering, data will be separated into baseline-corrected and nonoverlapping epochs time-locked to the target onset. Epochs containing high amplitude/frequency and muscle or other irregular artifacts will be removed by visual inspection. Only artifact-free epochs from correct trials will be selected for averaging. The existence of blinks and other ocular movements will not be a criterion for epoch rejection. This kind of artifact will be eliminated using Independent Component Analysis (ICA) [92–98]. After submitting EEG data to ICA decomposition, artifactual components will be removed by inspection of their activity, scalp topography, and spectral power. The length of the epoch in the target-locked ERP will be 1100 ms, and 600 ms in the response-locked ERP. We focus on P2, N2, and P2b. Analyses will be centered on the posttarget and postresponse ERPs at the midline electrodes located at the frontal, central, and parietal lobes (Fz, Cz, and Pz) where the components of interest are usually maximum. P2 is a positive ERP component associated with retrieval of stimulus–response sets that will be measured between 150 and 300 ms. N2 will be measured at the most negative pick between 150 and 400 ms after target onset. P3b will be measured in the time window of 300–600 ms after target onset. This wave is associated with context updating and working memory (see [75, 76, 87]).

### Secondary outcomes

#### Assessment of emotional and affective well-being

##### The Positive and Negative Affect Schedule (PANAS)

The PANAS [99] is a self-report questionnaire designed to assess the affective state. It consists of two 10-item scales to measure both positive and negative affect. Positive affect reflects the point to which a person feels enthusiastic, active, and alert, with energy and rewarding participation. Negative affect represents a general dimension of subjective distress and unpleasant participation that includes a variety of aversive states, such as disgust, anger, guilt, fear, and nervousness. Participants in the PANAS respond to a 20-item test using a 5-point scale that ranges from very slightly or not at all (1) to extremely (5). We use the Spanish version [100] that provides good consistency and reliability indexes, and also confirms the original two factors of the questionnaire. The reliability (Cronbach’s α) and validity, both convergent and discriminant, have also been corroborated in the elderly Spanish population [101].

The outcomes of interest are the mean score per group of positive and negative affect assessed with the PANAS questionnaire at three time points: pretest, posttest, and follow-up. The specific metric will be the change from baseline.

##### The Life Satisfaction Index (LSI)

The LSI [102] is a 20-item self-report questionnaire to measure psychological well-being in older adults. The instrument consists of five subscales, including zest for life (four items), resolution and fortitude (five items), congruence between desired and achieved goals (three items), positive self-concepts (three items), and mood tone. Respondents express their agreement or disagreement with the statements based on a 3-point Likert scale (agree = 2 points; disagree = 1 point; and “don’t know” = 0 points). The higher the overall score, the higher the individual’s life satisfaction.

The outcome of interest is the mean score per group of the individual’s life satisfaction assessed with the LSI questionnaire at three time points: pretest, posttest, and follow-up. The specific metric will be the change from baseline.

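### The printed Life Satisfaction Index key scores an undecided answer below a dissatisfied one, so the total is not ordered by life satisfaction as the protocol says

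*Protocol article*

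**What the plan says.** The Life Satisfaction Index (LSI) section of the protocol article, under Secondary outcomes, states that the LSI "is a 20-item self-report questionnaire to measure psychological well-being in older adults". On the response format it says: "Respondents express their agreement or disagreement with the statements based on a 3-point Likert scale". The points are "agree = 2 points; disagree = 1 point", and the undecided option closes the list with "don’t know” = 0 points". The direction is then fixed: "The higher the overall score, the higher the individual’s life satisfaction". The use of the total is also fixed: "The outcome of interest is the mean score per group of the individual’s life satisfaction assessed with the LSI questionnaire", at three time points, and "The specific metric will be the change from baseline".

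The Statistical analysis section plans repeated-measures ANOVA for secondary outcomes. No other section gives a different LSI key or a separate rule for *don't know*.

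**The concern.** A summed score rises with satisfaction only if each item's points do. On an agree/disagree statement, *don't know* takes neither side: it is a middle answer or an uninformative one. The printed key makes it the lowest answer, below *disagree*.

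A participant who goes from undecided to openly dissatisfied then gains points, and one who goes from dissatisfied to undecided loses them. The total mixes well-being with readiness to give a definite answer. Because the same questionnaire is repeated three times and analysed as change, a drift in the use of *don't know* would be read as a change in life satisfaction.

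**Working it through.** The article gives no LSI range, expected mean or variance, so there is no stated figure to reproduce. The inputs, all from the LSI section, are 20 items and the key 2 / 1 / 0 for agree / disagree / don't know.

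**1. Order within one item, key applied as printed.**

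| Item wording | Satisfied answer | Undecided | Dissatisfied answer | Dissatisfied minus undecided |
|---|---|---|---|---|
| Agreement means satisfied | agree = 2 | 0 | disagree = 1 | +1 |
| Agreement means dissatisfied | disagree = 1 | 0 | agree = 2 | +2 |

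In both rows the step from undecided to dissatisfied earns points. Swapping the two explicit values on negatively worded items would give satisfied = 2 and dissatisfied = 1, but undecided stays at 0, so the order is still broken.

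**2. The total.** Let *a*, *d* and *k* be the numbers of agree, disagree and don't-know answers, with *a* + *d* + *k* = 20.

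- Printed key: T = 2*a* + *d* = 20 + *a* − *k*.
- Comparison key with *don't know* as the midpoint (agree 2, don't know 1, disagree 0; illustrative, positively worded items assumed): M = 2*a* + *k*.

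The count *k* enters with opposite signs.

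| Answers (*a*, *d*, *k*) | Printed T | Midpoint M |
|---|---|---|
| 20, 0, 0 | 40 | 40 |
| 0, 20, 0 | 20 | 0 |
| 0, 0, 20 | 0 | 20 |
| 10, 10, 0 | 30 | 20 |
| 10, 0, 10 | 20 | 30 |

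Rejecting every statement scores half the maximum; being undecided on every statement scores zero.

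**3. An illustrative change.** Move 5 items from *don't know* to *disagree*.

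- Printed key: 5 × (+1) = +5, which is 5/40 = 12.5% of the range.
- Ordered key, all 5 positively worded: 5 × (−1) = −5.
- Ordered key, *m* of the 5 negatively worded and scored by their own direction: *m* − (5 − *m*) = 2*m* − 5. This runs from −5 (*m* = 0) to +5 (*m* = 5).

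The sign reversal in this example therefore depends on item wording. What does not depend on wording is step 1: five moves from undecided to the dissatisfied answer score between +5 (all positively worded) and +10 (all negatively worded), where the ordered key gives −5.

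**4. When it does no harm.** With positively worded items and *k* = 0 throughout, T = 20 + *a* and M = 2*a*, so T = 20 + M/2. That is a linear rescaling with the same order and the same *F*-test.

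**5. Extent of disagreement between the keys.** Over all 231 possible (*a*, *d*, *k*) profiles, with positive wording, the two keys rank 8,140 of 25,135 strictly ordered pairs in opposite directions (32%). Profiles are counted unweighted, so this describes the keys and does not estimate a share in trial data.

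**The case against.** Several points can be made for leaving this alone.

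- **It may be a slip in the article.** The scoring in use may follow the cited instrument. That is possible and cannot be checked from the document. But this is the only key given and it is explicit, so it needs correcting whether the text or the scoring is at fault.
- **Reverse-keying.** A reader might infer that the plan wrongly omits reverse-keying. The document does not support this: no items are printed, and item direction is commonly left to the scoring manual. The point here does not need it.
- **Treatment effect.** A reader might infer that the LSI group comparison will come out with the wrong sign. That is not shown. From T = 20 + *a* − *k*, the arm difference in mean change is distorted through the arm difference in mean change in *k*. If *don't know* use shifts alike in all four arms, that part cancels. Cancellation would protect the contrast from bias; it would not make the score measure what the protocol says.
- **Rarity.** *Don't know* may seldom be chosen. Its frequency is not given, so the effect could be small.
- **Standing of the outcome.** The LSI is one of several secondary outcomes and does not enter the sample size. This stands and limits the importance of the point.

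**Conclusion.** The point holds. As printed, the LSI key contradicts the claim that a higher total means higher life satisfaction, because an undecided answer scores below the explicitly dissatisfied one under either item wording. Change from baseline in this outcome can partly reflect changes in the use of *don't know*.

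The +5 versus −5 example assumes positively worded items. The size in the trial is unknown because it depends on how often *don't know* is chosen; on positively worded items it is nil if it never is. The conclusion is confined to one secondary outcome. Primary outcomes, sample size and type I error are unaffected. It should be corrected because a stated scoring rule for a named outcome is wrong as written and is cheap to put right.

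**What to change.** 1. Check the printed key against the cited instrument and state the key actually used.
2. Correct it so that, on every item, the satisfied answer scores highest, the dissatisfied answer lowest, and *don't know* not below the dissatisfied answer. Satisfied 2, don't know 1, dissatisfied 0 is one example; the instrument's own key should decide.
3. If any items are negatively worded, apply the instrument's item direction and say which items they are.
4. Keep item-level responses and re-score all three assessments from them before the LSI is analysed.

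The cost is a few sentences in the protocol and a change in scoring syntax. No new data are needed if item-level responses have been kept.

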#### Assessment of physical condition

##### The Short Physical Performance Battery (SPPB)

The SPPB [103] measures functional status and physical performance. First described in 1994, it is a composite measure assessing walking speed, standing balance, and sit-to-stand performance. The SPPB is calculated from three components: the ability to stand for up to 10 s with feet positioned in three ways (together side by side, semi-tandem, and tandem); time to complete a 3-m or 4-m walk; and time to rise from a chair five times.

Lower-extremity physical performance is assessed in the study with a composite measure of walking speed, standing balance, and sit-to-stand performance. The outcome will be the performance mean in the battery of the groups at three time points: pretest, posttest, and follow-up. The specific metric will be the mean change from pretest to the other time points.

##### The 6-Minute Walk Test (6MWT)

The 6MWT [104] is commonly used to assess exercise capacity. The participant walks for 6 min as fast as possible. The primary outcome is the distance completed. The test is administered in accordance with the protocol endorsed by the ATS [105]. The test is performed on a straight 30-m corridor and all participants receive standardized scripted instructions and scripted phrases of encouragement each minute during the test. Besides the distance, monitored parameters are changes in oxygen saturation (SpO_2_), and pretest and posttest dyspnea and fatigue using the Borg scale [106].

Functional capacity is assessed in the study with the 6MWT. The outcome measure will be the mean absolute value in the test obtained by the groups at three time points: pretest, posttest, and follow-up. The specific metric will be the mean change from pretest to the other time points of the study.

### Statistical analysis

All data from participants with complete baseline assessment and who attended at least one training session will enter into a primary intention-to-treat analysis. For the secondary per-protocol analysis, only the data of participants with a complete cognitive assessment and an attendance rate ≥ 70% will be considered.

Executive functions (set shifting, maintenance, inhibitory control) and memory functions (short-term, visual, and verbal immediate and delayed memory) will be assessed at pretest, posttest, and follow-up. The statistical analysis corresponding to the behavioral results will be carried out with the SPSS statistical package for Windows (SPSS 25.0; IBM Corporation). Results will be considered significant at *p* < 0.05, with Bonferroni-corrected post hoc tests performed as appropriate. We will explore the missing data to ascertain their pattern and will apply an adequate technique of multiple imputation. Repeated ANOVA measures will be conducted with four groups (multidomain training, cognitive training, exercise training, active control) at three time points (pretest, posttest, follow-up) to test the primary hypothesis (i.e., differences in efficacy between interventions compared to the active control condition). Repeated ANOVA measures will also be performed to determine the effect of the interventions on secondary outcomes. To evaluate the effect size of the combined multimodal group versus each individual intervention group and the control arm, we will use multimodal regression with an interaction term. Electrophysiological data will be analyzed with CURRY 8.0.2, the EEGLAB toolbox [92], and the ERPLAB plugin for EEGLAB [98].

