### Primary outcomes: training effects on cognitive functions

#### Set-shifting

##### Memory-based task switching

Executive functions will be assessed with a memory-based task-switching paradigm. In this task [76, 87], digits from 1 to 9 (excluding number 5) are presented in white on a black background on the computer screen. A cue indicating the relevant task is presented simultaneously with the digit below the fixation point. The cue “NUM” indicates a numerical task (smaller or greater than 5), “PAR” the parity task (odd vs. even), and “TAM” (a diminutive for Spanish “tamaño” (size) font) the font-size task (small vs*.* large). Each stimulus is presented in small (7 mm × 10 mm) and large (12 mm × 18 mm) size. Participants will perform three single and two mixed blocks. In the single blocks, they have to process digits according to the one-task rule (i.e., numerical, parity, or font-size task only). In the memory-based mixed blocks, participants have to switch between different tasks within the block. In the cue block they are instructed to switch the rule after every three trials in the following order “NUM–NUM–NUM–PAR–PAR–PAR–TAM–TAM–TAM”, while a cue is presented in every trial simultaneously with the digit. In the memory block, participants are instructed to switch the rule after every three trials in the same order, while “XXX” instead of a cue is presented; that is, participants have to keep track of the trial sequence in their working memory. When three consecutive errors are made, or no response is given, cues are presented on three consecutive trials to help participants to find the track. Single blocks consist of 35 trials each, and two mixed blocks consisting of switch and no-switch trials: a cued block (90 trials) and a memory block (90 trials). The mixed blocks are equal with respect to the stimulus type, response type, and frequency of task switch (33.3%). The stimulus–response mapping of the three tasks is overlapping; that is, responses according to “smaller than 5”, “even”, and “small size” are assigned to the left key and “larger than 5”, “odd”, and “large size” to the right key. The assignment will be counterbalanced across participants. The outcomes of interest are mean reaction times (RTs) between groups corresponding to correct trials at pretest, posttest, and follow-up time points. The specific metric will be the change from baseline.

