#### Processing speed and flexibility

##### Trail Making Test (TMT)

The TMT is a neuropsychological test of visual attention and task switching. The test comprises two parts (A and B). Each part consists of 25 circles distributed over a sheet of paper. In Part A, the circles are numbered 1–25, and the participant draws lines to connect the numbers in ascending order. In Part B, the circles include both numbers (1–13) and letters (A–L); the task consists of connecting the circles in an ascending pattern, but with the added task of alternating between the numbers and letters (i.e., 1–A–2–B–3–C, etc.). The total times in seconds for Parts A and B represent the TMT-A and TMT-B direct scores. Scores of TMT-A account for perceptual speed, whereas the B–A difference score is an indicator of task-switching abilities. The outcomes of interest are the mean time scores of the difference score, TMT-B minus TMT-A, to assess task switching between groups at pretest, posttest, and follow-up time points. The specific metric will be the change from baseline.

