#### Working memory

The *N*-back task is a continuous performance task to assess maintenance and updating of information in working memory. This task has been used with older adults [88–90]. Participants are presented with a sequence of stimuli (consonant letters), and indicate whether the last stimulus matches the one presented “*n*” trials back by pressing one of two keys (one for “yes” or another for “no”). We used a three level *N*-back task. In the 0-back condition, the letter X is the target. We include the 0-back condition as an index of perceptual-motor speed to control for the role of speed of processing in working memory performance. In the 1-back condition, participants have to remember the stimulus presented just before the current stimulus; in the 2-back level, they have to remember the stimulus presented two positions before. Each participant first performs a practice block of 17 trials at each level, followed by the experimental trials. Each level contains three blocks of 27 trials (81 trials per level), yielding a total of 243 trials. Each block of 27 trials consists of 17 “nontargets” (“no” response) and 10 “targets” (“yes” response). The outcomes of interest are the mean accuracy between groups as assessed by Hits–False alarms. The specific metric will be the change from baseline (pretest) to posttest and follow-up.

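### Six or more co-equal behavioural primary outcomes are judged at p < 0.05, and the only stated correction, Bonferroni for post hoc tests, does not act across them

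*Protocol article*

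**What the plan says.** Under the heading "Primary outcomes: training effects on cognitive functions" the protocol article describes, in turn:

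- memory-based task switching: "The outcomes of interest are mean reaction times (RTs) between groups corresponding to correct trials"
- the Trail Making Test: "The outcomes of interest are the mean time scores of the difference score, TMT-B minus TMT-A"
- N-back: "The outcomes of interest are the mean accuracy between groups as assessed by Hits–False alarms"
- Stroop reaction time
- WMS-III Faces, immediate and delayed
- WMS-III Word-Pair List, immediate and delayed recall plus a recognition task

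The electrophysiological measures follow before the Secondary outcomes section begins: "Analyses will be centered on the posttarget and postresponse ERPs at the midline electrodes located at the frontal, central, and parietal lobes".

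The Statistical analysis section gives the test and the threshold: "Repeated ANOVA measures will be conducted with four groups" at three time points, and a significance level of p < 0.05, "with Bonferroni-corrected post hoc tests performed as appropriate". For the electrophysiological data it names only software. No primary outcome is given precedence, and no composite or testing order is stated. The Sample size section uses an undivided alpha of 0.05 and ties it to no particular outcome.

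**The concern.** A post hoc correction limits error among the comparisons that follow one ANOVA. It does nothing about running the same ANOVA on several outcomes that all carry primary status. A trial in which no training works could then, with probability well above 5%, report that training improved a primary outcome, and which outcome to emphasise would be open. The 0.05 in the plan is the error rate of one test on one outcome. It is not the error rate of the statement that the intervention improved executive control or memory.

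This is not a detail merely left to an analysis plan. The protocol states a significance rule and says where the correction applies.

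**Working it through.** **Inputs.** Alpha is 0.05 per result (Statistical analysis). The number of behavioural primaries, m, comes from the primary-outcomes section:

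- m = 6 counts instruments: task switching, TMT, N-back, Stroop, Faces, Word Pairs.
- m = 8 splits Faces and Word Pairs into immediate and delayed.
- m = 9 adds word-pair recognition.

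The correlation between outcomes is not in the document. It is assumed exchangeable and varied from 0 to 0.8.

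**The plan's own figures.** The protocol states no family-wise error rate to reproduce. Its sample-size figure is 124 before dropout. A one-way four-group F-test with f = 0.38, alpha 0.05 and power 0.80 gives 80, so 124 is not reproduced by that test; at N = 124 its power is about 0.95. The dropout step is consistent: 124/0.88 = 140.9, so 141, which becomes 144 with 36 per arm. The gap between 80 and 124 is a separate matter and does not affect the error rates below.

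**Error rate, independent outcomes.** P(at least one p < 0.05) = 1 − 0.95^m.

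- m = 6: 1 − 0.7351 = 26.5%
- m = 8: 1 − 0.6634 = 33.7%
- m = 9: 1 − 0.6302 = 37.0%

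**Error rate, correlated outcomes.** Simulation of m correlated four-group tests (3 degrees of freedom, chi-square approximation, 40,000 runs, all nulls true):

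| Assumed correlation | m = 6 | m = 8 | m = 9 |
|---|---|---|---|
| 0 (formula) | 26.5% | 33.7% | 37.0% |
| 0.3 | 24.5% | 30.2% | 33.1% |
| 0.5 | 21.5% | 25.8% | 28.0% |
| 0.7 | 17.3% | 20.0% | 21.4% |
| 0.8 | 14.4% | 16.6% | 17.8% |

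This allows one test per outcome. That is lenient: a 4 × 3 ANOVA yields both a group and a group-by-time test, and the text does not say which decides.

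**Cost of control.** The first Holm step is 0.05/6 = 0.0083, 0.05/8 = 0.00625 or 0.05/9 = 0.0056. For the one-way four-group F-test at f = 0.38 and 80% power, the total needed is 117, 123 or 125. Expected completers are 144 × 0.88 = 126.7.

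**Whether Holm inside each contrast is enough.** The General procedure section implies five contrasts: multidomain against each of two single-domain arms, and three arms against active control. With eight outcomes, all nulls true and Holm applied separately inside each contrast, simulation gives at least one false positive in about 20% of trials (correlation 0), 18% (0.3) or 16% (0.5). Correction must therefore act on one overall test per outcome, or on outcomes and contrasts together.

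**The case against.** **Multiplicity detail is often left to an analysis plan, and none is shown here.** This stands as a reason for restraint. It does not dispose of the point, because the protocol itself fixes the threshold and confines the correction to post hoc tests.

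**The size of the inflation depends on the count and the correlation.** This stands. Faces and Word Pairs are each given one hits-minus-false-alarms mean as outcome of interest, so the text secures only six outcomes; eight or nine is a reasonable reading, not a floor. Cognitive scores are likely to be positively correlated, which lowers the figure, though even six outcomes at correlation 0.8 give about 14%.

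A reader might also infer more than the text supports:

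- *That the ERP measures are each tested uncorrected at 0.05, pushing the error rate above 40%.* The threshold sentence follows the one on behavioural results, and no ERP test or threshold is given. Their place under the primary heading makes their status unclear and shows no more than that.
- *That no time point is set.* The General procedure section puts the main question at posttest. What remains open is the outcome and the family.
- *That testing posttest and follow-up inflates the error further.* One group-by-time test covers both later visits, and comparisons after it fall under the stated Bonferroni.

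**Conclusion.** The concern holds for the behavioural primary outcomes. As written, the chance of at least one false-positive behavioural primary is about 26–37% under independence, 21–28% at correlation 0.5 and 17–21% at 0.7. These figures assume that no intervention has any effect, that there is one overall test per outcome, that there are six to nine outcomes, and that correlation is exchangeable. The correlation values are not from the protocol. Every combination examined is well above 5%.

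No figure is attached to the ERP measures, because their testing is not stated. The matter should be settled before the data are analysed, all the more because the Randomization and blinding section says that data analysis will not be blinded. That fact gives no ground to infer that results would be selected.

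**What to change.** In the Statistical analysis section:

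1. Define the confirmatory family as the listed behavioural primary outcomes, with one named score for each. Task switching needs this especially, since it has single, cued and memory blocks and both switch and no-switch trials.
2. Name one deciding test per outcome: the group-by-time test, or the four-group comparison at posttest.
3. Apply Holm across outcomes to that test. Test group contrasts only for outcomes that pass, with the Bonferroni correction already stated. Alternatively, apply Holm over all outcome-by-contrast tests together; with eight outcomes and five contrasts that is 40 tests and a first step of 0.05/40 = 0.00125.
4. Label the ERP measures, already the second objective in Objectives and hypotheses, and the follow-up comparisons as secondary.

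This is more than a wording change. It re-designates outcomes in a registered trial that is already recruiting, so it should be a dated amendment.

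The statistical cost is lower power per outcome, with a first Holm step of about 0.0056–0.0083 on the first route. At the protocol's own f = 0.38 the one-way test needs 117–125 participants, just within the roughly 127 expected completers. That margin is thin, holds only if f = 0.38 is realistic, and does not carry over to the group-by-time test, whose power depends on a within-person correlation that the protocol does not give. The 40-test route costs more.
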